### Criteria for discontinuing or modifying allocated interventions {11b}

If the participant shows signs/symptoms of pulpal involvement and requires other treatment modalities, treatment will be discontinued and the participant data will be excluded from the study. However, they will still be followed up for safety assessment.

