This approach has been increasing in dentistry, being associated with antimicrobial photodynamic therapy (aPDT) [4–6]. The use of red/yellowish dyes is being researched for their application in aPDT. *Bixa orellana* is a plant native to Brazil. From its seeds, it is possible to extract a dye, popularly known as “urucum.” This dye has important antioxidant and antimicrobial activities, and recent studies have shown its potential as a photosensitizer in aPDT [3, 6, 11, 12]. Due to its positive characteristics, especially regarding the lack of mutagenic and cytotoxic activity and antimicrobial effect, the *Bixa orellana* extract (Fórmula e Ação, São Paulo, SP, Brazil) could be considered a suitable candidate as a photosensitizer. Using a dye with these characteristics would make aPDT more accessible [6, 13].

There are no controlled clinical trials in the literature that confirm the effectiveness of this type of therapy on deep caries-affected dentin associating Papacarie™ and aPDT with *Bixa orellana* extract, especially in the deep caries lesion. The justification for performing the treatment with Papacarie™ associated with aPDT using the *Bixa orellana* extract is to reduce the risk of pulp exposure in permanent teeth and increase the antimicrobial activity.

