### Eligibility criteria {10}

#### Inclusion criteria

Adequate health with no systemic conditions (ASA 1);Adequate cooperation (scores 1 or 2 in Wright’s modification of Frankl’s behavior scale);Clinically presenting at least 1 permanent molar with an acute, active caries on the dentin not surpassing 2/3 and only involving the occlusal face, with direct view and access as well as no clinical or radiographic signs of pulp involvement. It is not intended to include more than one tooth per participant;Six to 12 years of age;Scores 3 (localized enamel breakdown due to caries with no visible dentine), 4 (underlying dark shadow from dentine), or 5 (distinct cavity with visible dentine) of the International Caries Detection and Assessment System criteria (ICDAS), in the occlusal surface; andThe setting to access these criteria will be during a clinical and radiographic examination, performed in the pediatric clinic of the dentistry course of Paulo Picanço School of Dentistry.

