#### Clinical evaluation

This is one of the primary outcomes of the study. The clinical evaluation will be performed by a researcher blinded to the different treatment groups. The criteria used for the evaluation will be the retention of the restorative material in the cavity and the occurrence of secondary caries. The evaluation scores will be based on the criteria below. Digital photographs of the restorations will also be taken and serve to complement the clinical and radiographic findings. The visual demonstration will contribute to any necessary clarifications and facilitate the discussion and documentation of the cases. Thus, digital photographs will be taken of all teeth in the different groups before and after the interventions. We believe participants will be present for the follow-ups due to concerns and other possible treatments in the clinic.0 = present; no defects;1 = present; small marginal defects measuring less than 0.5 mm in depth; no need for repair;2 = present; small marginal defects measuring 0.5 mm to 1mm in depth; need for repair;3 = present; large marginal defects measuring 1 or more mm in depth; need for repair;4 = absent; restoration nearly or completely lost; need for treatment;5 = absent; additional treatment having been performed for some reason;6 = tooth absent for any reason;7 = present; surface wear measuring less than 0.5 mm in depth; no need for replacement;8 = present; surface wear greater than 0.5 mm in depth; need for replacement; and9 = impossible to diagnose.

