### Sample size {14}

The sample size was calculated based on a previous study in the literature [16, 17] (Fig. 2), considering the expected difference and standard deviation and weighting colony-forming units (CFU) of bacteria. For the statistical calculation, paired samples were considered, with α=5% and an 80% test power. The minimum number in this clinical trial was determined to be 34 teeth per group. Therefore, 40 teeth per group will be recruited to compensate for possible dropouts during the experimental period. G*Power 3.1 was used to perform the calculations (Fig. 3).

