### Methods in analysis to handle protocol non-adherence and any statistical methods to handle missing data {20c}

No losses greater them 5% of the sample are expected, and if they happen, pairwise deletion will be used.

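### Children who develop pulpal involvement and need other treatment are removed from the analysis, so treatment failures are deleted after randomisation

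*Protocol article*

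**What the plan says.** The rule is in the protocol article, Criteria for discontinuing or modifying allocated interventions {11b}. Its trigger is "If the participant shows signs/symptoms of pulpal involvement and requires other treatment modalities". Its consequence is that "treatment will be discontinued and the participant data will be excluded from the study". The one thing kept is stated next: "However, they will still be followed up for safety assessment".

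Other sections bear on it:

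- **Inclusion criteria:** the tooth must show "no clinical or radiographic signs of pulp involvement".
- **Background and rationale {6a}:** the experimental treatment is justified as a way "to reduce the risk of pulp exposure in permanent teeth and increase the antimicrobial activity".
- **Outcomes {12}:** the microbiological, radiographic and clinical evaluations are all primary. The radiographic one includes periapical integrity up to 12 months.
- **Clinical evaluation:** one category of the primary score is "5 = absent; additional treatment having been performed for some reason".
- **Methods in analysis to handle protocol non-adherence and missing data {20c}:** "No losses greater them 5% of the sample are expected, and if they happen, pairwise deletion will be used".

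No section brings the excluded children back, either through an as-randomised analysis or by scoring them as failures.

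**The concern.** Pulpal involvement that needs other treatment is a poor result of caries treatment. Dropping the child's data because of it makes membership of the analysis set depend on what happened after allocation.

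Two things are at stake. First, success is overstated in each arm where such events occur. Second, if the events are more frequent in one arm, the comparison is no longer between the groups that randomisation formed, and a real difference in the most serious failures can vanish from the primary results. Unequal rates are plausible: Group 1 has carious dentin removed with a drill, while Groups 2 to 4 leave carious tissue on the pulp floor (Intervention description {11a}).

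The rule is also wider than it needs to be. It covers all of the participant's data, so colony counts already obtained at the treatment visit are discarded when the event comes later.

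**Working it through.** **Step 1. Is the event post-randomisation?** Eligibility is settled by a clinical and radiographic examination that must show no pulp involvement. The envelope is drawn at the time of treatment (Sequence generation {16a}). Involvement found during caries removal or at follow-up therefore comes after allocation.

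**Step 2. Does it bear on a primary outcome?** It is not named as an endpoint. It enters through periapical integrity and through the clinical score, where category 5 could record a tooth that received additional treatment. Section {11b} takes such a tooth out before it can be scored.

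**Step 3. What does exclusion do to a failure proportion?** The document states no pulpal failure rate, so there is no figure to reproduce and the rates below are assumptions. Let p be the proportion of an arm with pulpal involvement needing other treatment, and q the proportion of other failures among the remaining teeth, taken as equal in the two arms.

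- Events counted: failure = p + (1 − p)q
- Events excluded: failure = q
- Understatement within an arm: p(1 − q)
- Between-arm difference: (1 − q)(p_B − p_A) if counted, 0 if excluded

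With q = 10% and 40 teeth per arm:

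| p, arm A vs arm B | Teeth excluded | Failure if counted | Difference | Failure if excluded | Difference |
|---|---|---|---|---|---|
| 5% vs 5% | 2 vs 2 | 14.5% vs 14.5% | 0 | 10% vs 10% | 0 |
| 5% vs 15% | 2 vs 6 | 14.5% vs 23.5% | 9.0 points | 10% vs 10% | 0 |
| 5% vs 20% | 2 vs 8 | 14.5% vs 28.0% | 13.5 points | 10% vs 10% | 0 |

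For example, 0.15 + 0.85 × 0.10 = 0.235. With q = 0, the last two differences would be 10 and 15 points. In the first row the comparison is unbiased, but failure is still understated by 0.05 × 0.90 = 4.5 points in both arms.

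**Step 4. Continuous outcomes such as radiographic density.** Suppose the excluded fraction p of one arm is the worst p on a normally distributed outcome. The arm's mean then improves by φ(c)/(1 − p) standard deviations, where c is the 1 − p normal quantile. If the outcome correlates only 0.5 with the failure tendency, the shift is half of that.

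| p excluded | Shift, full tracking | Shift, correlation 0.5 |
|---|---|---|
| 5% | 0.11 SD | 0.05 SD |
| 10% | 0.20 SD | 0.10 SD |
| 15% | 0.27 SD | 0.14 SD |
| 20% | 0.35 SD | 0.17 SD |

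**Step 5. Colony counts.** The second sample is taken in the treatment session, straight after removal of carious tissue. If the pulpal event appears at a later visit, both counts exist and the rule throws them away. If it is found during removal, the second count may not exist.

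**The case against.** The best defence is that the rule may be aimed at pulpal involvement discovered at treatment. Stopping treatment fits an event in the session better than one months after restoration, and pulp involvement is also an exclusion criterion. Part of this stands: not every trigger need be a failure caused by the allocated treatment. But the wording is not limited to that case. Even then the envelope has been drawn and the treating researcher knows the arm, so removing the child is still a selection after allocation.

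A second defence is that an article leaves the analysis set to a fuller document. That would excuse silence. Here the article states a rule.

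Several stronger readings are tempting, and the document does not support them:

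- **The direction of bias is known.** A reader might infer that one technique is favoured, or that the arm with more failures will look better than the other. No rates are given. Exclusion makes an arm look better than it was, not necessarily better than its comparator.
- **Codes 5 and 6 exist to record pulpal failure.** The score concerns restoration retention and secondary caries. Code 5 could capture these cases; code 6 covers an absent tooth for any reason. Neither is specific to the pulp.
- **Colony counts are always complete before the event.** They are not if involvement is found during removal.
- **The follow-up data will exist anyway.** Safety follow-up does not promise trial radiographs or clinical scores.
- **The loss figures contradict each other.** The sample size section says "40 teeth per group will be recruited to compensate for possible dropouts during the experimental period". The reserve over the minimum of 34 is 6/40 = 15%, against an expected loss of at most 5%. A reserve larger than the expected loss is ordinary caution.
- **Pairwise deletion must give way to a mixed model.** That is a separate choice of method, and this point does not depend on it.

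**Conclusion.** The concern holds in a limited form. As written, {11b} deletes data because of a post-randomisation event that can be a treatment failure and that bears on two primary outcomes. Success is overstated in every arm where such failures occur; that follows from the rule itself. Bias between arms depends further on event rates, or the kind of child excluded, differing by arm. This is plausible from the removal techniques but not shown.

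The size cannot be fixed from the document. Under the assumed rates above, a difference of 9.0 to 13.5 points in failure would disappear from the analysis; at equal rates nothing is lost from the comparison and 4.5 points from each arm's failure rate. For colony counts the bias is probably smaller, since they are taken in the treatment session, but discarding those already obtained serves no purpose.

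This is worth correcting before analysis. It concerns only the handling of data. Whether and when treatment stops is a clinical matter and is not at issue.

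**What to change.** In {11b}, replace the clause "treatment will be discontinued and the participant data will be excluded from the study", as far as it concerns data, with an analysis rule along these lines:

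- All randomised teeth are analysed in their allocated arm.
- Any colony-count samples obtained are kept. A second sample not taken because of the event is reported as missing, with the reason.
- Pulpal involvement needing other treatment counts as failure in the clinical and periapical outcomes from the visit at which it is found.
- Radiographic density observed before the event is kept.
- The number and timing of these events are reported by arm.

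Then reconcile {11b} with the Clinical evaluation section, saying how such a tooth is scored, and with {20c}, saying that these children are not losses to be handled by pairwise deletion.

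The cost is protocol wording, one table of events by arm and a little extra analysis. The sample size does not change. Counting the event as failure needs only the event itself, which the planned safety follow-up should capture, so the rule works even if later trial radiographs and scores are not taken.

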### Strategies to improve adherence to interventions {11c}

Participants will be enrolled for treatment at the pediatric clinic of the dentistry course of Paulo Picanço School of Dentistry (Fortaleza-Ceará, Brazil). As they will already be in treatment, we believe this will improve adherence. They will also be told about the importance of the follow-up to complete the research data.

### Relevant concomitant care permitted or prohibited during the trial {11d}

Children involved in the study may present caries involving enamel, deficient restorations, small carious lesions on dentin with no access for manual scalers, hidden caries, sign or symptom of pulp involvement, clinical impossibility of restoration, evidence of pulp involvement, or carious lesion extending beyond 2/3 of dentin in other teeth, which are not involved in the study. In these cases, the researchers will provide the necessary care for these other conditions.

### Provisions for post-trial care {30}

No major harms are expected, but possible intercorrences, such as tooth pain, will be monitored and recorded. Any additional assistance participants may need, will be provided.

### Outcomes {12}

For the treatment of caries lesions to be considered successful, it should be able to remove infected tissue and microorganisms in a sufficient amount, so that, in the control session, the teeth that were once infected do not show any signs of remaining infected tissue beneath the restorative material. Consequently, the microbiological evaluation had been chosen as the primary outcome. However, factors such as the radiological exam and the clinical aspects are also important for the control section, to show the presence or lack of success. Therefore, the microbiological, radiographic, and clinical evaluations should be considered as primary outcomes.

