#### Specific objectives

To investigate the efficacy of photodynamic therapy with *Bixa orellana* and Papacarie™ with regard to microbiological (counting of colony-forming units before and after treatments – CFU), radiographic (integrity of the periapical area and eventual changes in the radiolucent zones), and clinical aspects (retention of the restorative material in the cavity and occurrence of secondary caries) (primary objective);To evaluate the antimicrobial effect of aPDT on caries-affected dentin in permanent teeth (secondary objective);To perform a radiographic evaluation of the remaining dentin and radiographic density at 6 evaluation times, over a 12-month period (secondary objective); andTo evaluate the need for local anesthesia during intervention and the degree of pain/discomfort (with a face scale) of children during the different procedures (secondary objective).

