#### Hypothesis

Hypothesis (H0): The administration of Papacarie™ and aPDT with *Bixa orellana* extract is not effective in the treatment of caries-affected dentin in permanent teeth.

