### Trial design {8}

This is a study protocol for a randomized (1:1), single-blind (outcome assessors, only), parallel groups, equivalence, one-center, phase 2, controlled clinical trial. Figure 1 shows a schematic diagram and is the Standard Protocol Items: Recommendations for Interventional Trials (SPIRIT) figure.

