## Interventions

### Explanation for the choice of comparators {6b}

The use of a drill, which is the conventional and most commonly used method, will be compared with the use of Papacarie™ with or without the *Bixa orellana* extract, and with or without the irradiation for aPDT. This study will show which of these treatments will be more efficient with regard to microbiological, radiographic, and clinical aspects. The models, types, and details of all instruments have been detailed upon the first appearance in the text.

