## Statistical methods

### Statistical methods for primary and secondary outcomes {20a}

The data will be stored in Excel datasets and analyzed statistically by employing different tests and considering a 5% level of significance. Only the researchers involved in the study will have access to the data, even if the study is discontinued. The results will be submitted to the Shapiro-Wilk test to check for normality. In case data distribution is normal, analysis of variance (ANOVA) will be used for both the dependent and independent variables. In case the data distribution is not normal, the Friedman test will be used for the dependent variables, followed by the Wilcoxon test as post hoc. For independent variables, the Kruskal-Wallis test will be used, followed by the Mann-Whitney test as post hoc. Pearson (for normal data) or Spearman (for non-parametric data) correlation coefficients may be calculated to determine correlations among the variables.

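### The trial is labelled equivalence but planned as a superiority trial with no margin, and it makes three outcome families primary with no rule for success

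*Protocol article*

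**What the plan says.** **Framework.**

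- Trial design {8} describes "parallel groups, equivalence, one-center, phase 2, controlled clinical trial". The text gives no margin, confidence-interval rule or equivalence test.
- Hypothesis: the null is that Papacarie with aPDT "is not effective in the treatment of caries-affected dentin in permanent teeth".
- Explanation for the choice of comparators {6b}: "This study will show which of these treatments will be more efficient with regard to microbiological, radiographic, and clinical aspects".
- Sample size {14}: the calculation was made "considering the expected difference and standard deviation and weighting colony-forming units (CFU) of bacteria", for paired samples at 5% and 80% power. It gave 34 teeth per group, raised to 40 for dropout.
- Statistical methods {20a}: a single 5% level for all tests. ANOVA is used for normal data and Friedman then Wilcoxon for non-normal dependent data. "For independent variables, the Kruskal-Wallis test will be used, followed by the Mann-Whitney test as post hoc".

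**Primary outcome.**

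- Outcomes {12} first says "Consequently, the microbiological evaluation had been chosen as the primary outcome" and, two sentences later, "Therefore, the microbiological, radiographic, and clinical evaluations should be considered as primary outcomes".
- The microbiological, radiographic and clinical subsections each then call their own evaluation primary.
- Specific objectives puts all three in the primary objective. It then lists "To evaluate the antimicrobial effect of aPDT on caries-affected dentin in permanent teeth (secondary objective", and adds residual dentin and radiographic density over 12 months as a further secondary objective.

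**The concern.** Equivalence is shown when a confidence interval lies inside a margin fixed in advance. With no margin, and with tests that only look for differences, the data cannot deliver that conclusion. The label nevertheless leaves room to present a null result as a positive finding.

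The primary claim is also undefined. With three primary families at 5% each and no statement whether one or all must be positive, the trial could be called successful by any of three routes. Two of those routes played no part in the sample size.

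The framework and the primary outcome are protocol decisions. A separate analysis plan could add a margin, but it could not make these sections of the protocol agree with each other.

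**Working it through.** **1. The plan's own figure.** The expected difference and SD are not in the text, and Figures 2 and 3 are not shown, so 34 per group cannot be reproduced from stated inputs. Solving backwards with the exact paired t-test (two-sided 5%), an assumed standardised paired difference of 0.5 gives n = 34 with power 0.808. Then 34/(1 − 0.15) = 40. The figure is consistent with a plain difference calculation in which no margin enters.

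**2. How often a real difference would be non-significant.** Assumption: a true between-arm difference of 0.5 SD, which the document does not state. Two-sided two-sample t-test at 5%, noncentrality d·√(n/2):

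- n = 40: 0.5·√20 = 2.236, df 78, power 0.598, so missed 1 − 0.598 = 40%.
- n = 34: 0.5·√17 = 2.062, df 66, power 0.529, so missed 1 − 0.529 = 47%.

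**3. What an equivalence claim would need.** Two one-sided tests at 5% each, true difference zero, normal approximation. The smallest margin with 80% power is (1.645 + 1.282)·√(2/n):

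- n = 34: 2.926 × 0.2425 = 0.71 SD.
- n = 40: 2.926 × 0.2236 = 0.65 SD.

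The text gives no margin to set against these. For assumed margins, n = 2·(2.926/margin)² gives 69 per group at 0.5 SD and 191 at 0.3 SD.

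**4. Error across the three families.** One omnibus test per family at 5%, no true effects: 1 − 0.95³ = 14.3% if independent. Simulation (20,000 runs, four groups of 34, ANOVA per family):

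| Correlation between outcomes | At least one false positive |
|---|---|
| 0 | 14.2% |
| 0.3 | 13.4% |
| 0.5 | 12.8% |
| 0.8 | 10.1% |

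**5. Error within one outcome.** Kruskal-Wallis at 5%, then unadjusted Mann-Whitney tests (20,000 runs, 34 per group):

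- All four arms equal: 4.8%, because the omnibus test must open first.
- One arm truly different (by 1.5 or 3 SD), the other three equal: the omnibus test opens almost always, and at least one of the three null pairs is falsely significant in 12.2%.

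The second case is plausible here. G1 is drill removal, whereas G2, G3 and G4 share Papacarie and partial removal. The pairs among G2 to G4 are also where the adjunct question in the title is answered.

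**The case against.** **Silence is not a statement.** The article is condensed, and post hoc adjustment is commonly left to an analysis plan. Statistical methods {20a} does not say that p-values will be unadjusted. This stands, so the 12% is conditional on no adjustment. The 10% to 14% does not depend on it: perfect correction inside each family still leaves three families at 5%.

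**Several primary outcomes are legitimate.** The Outcomes section can be read as a reasoned widening from one to three, and a rule that all three must succeed would remove the inflation. Both points are fair, but no such rule is stated, and the widening does not explain why the same content is also secondary.

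**The label may be one wrong word.** Nothing in the article says that a null result will be reported as equivalence. This is probably right, and it points to correcting the label rather than adding a margin. A margin in the missing figures cannot be excluded outright, but it would still clash with the null hypothesis, the aim and the tests.

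**Stronger readings that the document does not support.**

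- A reader might infer six free pairwise tests per outcome, with about 20% familywise error for four equal arms. That ignores the Kruskal-Wallis gate, which brings the figure to 4.8%. Mann-Whitney is also planned only for non-normal data, and no pairwise test is named after ANOVA.
- A reader might count six microbiological measures, six density visits and six clinical visits as 18 separate tests, giving 1 − 0.95¹⁸ = 60%. The plan does not prescribe a between-arm test at each visit; repeated data go to ANOVA or Friedman. The measures are also not independent, since the proportions share numerators and denominators.

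**Conclusion.** The point holds in two parts.

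First, the equivalence label contradicts the rest of the article, and no equivalence conclusion could follow from the plan as written. This rests on the text alone. The 40% and 47% illustrate the risk and depend on the assumed 0.5 SD.

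Second, the primary claim is not fixed. If success in any one family counts, the chance of a false-positive primary result is about 10% to 14% with one omnibus test each, depending on correlation. Within an outcome, error is near 5% when all arms are equal. It is about 12% among G2 to G4 when G1 alone differs and nothing is adjusted. It should not be claimed that the plan forgoes correction, or that error reaches 20% or 60%.

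Both parts should be settled before outcome data are analysed, because they determine what the trial can conclude.

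**What to change.** 1. In Trial design {8}, replace equivalence with superiority, and state that a non-significant result is not evidence of equivalence.
2. Name one CFU measure as the single primary outcome, namely the one behind the sample size, and make the radiographic and clinical outcomes secondary. The text does not say which count that was, so the investigators must identify it. If all three families stay primary, either test each at 0.05/3 = 0.0167 or require all three to succeed at 5%, with one named measure per family.
3. Name the lead between-arm comparison that answers the adjunct question. Which pair leads is the investigators' choice, provided it is fixed in advance. Test it first at 5%; if it succeeds, test the other pairs with Holm.
4. Align Specific objectives, Hypothesis, Trial design and Outcomes, so that no measure is both primary and secondary and the null names the arms compared.

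**Cost.** This needs a protocol and registry amendment. The article gives recruitment as 30 May 2022 to 30 April 2023 and was published in March 2023, so demoting declared primary outcomes is a substantive change and must be dated and justified. Non-lead comparisons lose a little power. Keeping three primaries costs more: splitting alpha lowers power in each family, and requiring all three gives 0.8³ = 51% joint power if each has 80% and they are independent. No extra visits or measurements are needed.
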